### Study design

#### In silico development

Our study will be conducted across three distinct centers located in Shanghai, Nanjing, and Suqian. The development of the multimodal AI system takes place in Shanghai. We will gather medical dialogues (at least 20 dialogues for each subspecialty) from 10 ophthalmic subspecialties, which include general ophthalmology, refractive diseases, strabismus, cornea, cataract, glaucoma, retina, neuro-ophthalmology, oculoplastics and orbital diseases, and ophthalmic emergencies (Supplementary Tables 1, 2). We will utilize these dialogues for prompt engineering to guide the ChatGPT diagnostic system. The brief process is as follows (Figure 2): When users input their chief complaints, the system will categorize them using a chief complaint classifier. Once classified, the system will automatically generate a tailored question list for the user and output each question from the list. After receiving the user's responses, both the chief complaints and all answers will be consolidated into the diagnostic prompt, which ultimately produces the user's diagnosis and triage results. Once the interactive system is developed, virtual cases (at least 50 cases for each disease) representing the top 1–5 diseases in each subspecialty will be introduced to assess diagnostic efficacy. For the diseases that fail to meet the predefined performance thresholds (sensitivity ≥ 90%, specificity ≥ 95%), we will develop an image-based diagnostic system tailored to the cases that have anterior segment images. Subsequently, we will integrate these components to establish a multimodal AI system, with a primary focus on image-based diagnosis, for the comprehensive evaluation of ophthalmic diseases (Figure 3).

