### Recruitment

For the *in silico* development stage, all cases will be recruited at the Eye & ENT Hospital of Fudan University. Specifically, researchers will record doctor-patient conversations at each subspecialty clinic. The conversations will undergo a curation process that involves the removal of filler words and irrelevant content, resulting in the creation of medical dialogues. Eligible medical dialogues will be continuously enrolled from June 1 to July 1, 2023. Regarding the anterior segment images, researchers will browse medical records and consistently gather images related to the top 1–5 diseases in each subspecialty from January 1, 2020 to July 1, 2023. The initial sample size consists of 20 dialogues per specialty and 50 images per disease, which is then adjusted according to the AI system's performance.

For the silent evaluation stage, data will be continuously gathered in Shanghai from July 10 to July 15, 2023, with a sample size of 100 cases. Two pre-trained researchers will serve as observers in outpatient clinics, ensuring they do not interfere with standard management procedures. Upon obtaining the patients' consent (as detailed in Supplementary material 2), the researchers will collect the patients' medical information and enter it into the system. For patients who are prescribed with anterior segment imaging test by outpatient clinic doctors, the researchers will collect the images from the electronic medical system.

For the early clinical evaluation stage, eligible participants will be continuously recruited at three distinct sites. The Shanghai site serves as an internal validation dataset, with data collection spanning from July 21 to August 20, 2023. The Nanjing and Suqian sites function as external validation dataset, with data collection scheduled from August 21 to August 31, 2023. Each center will be staffed with two pre-trained researchers. These researchers will be responsible for patient recruitment across various subspecialty clinics within their respective centers. Once patients provide their consent (as detailed in Supplementary material 4) to participate in the study, the researchers will gather medical history and acquire anterior segment images. Following this, outpatient physicians will proceed with clinical diagnosis and treatment.

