### Sample size calculation

In the *in silico* development stage, the sample size is adjusted based on AI system performance. Initially, each subspecialty involves 20 medical dialogues, with 80% for training ChatGPT and 20% for validation. If ChatGPT cannot generate inquiries, diagnoses, and triage results in the validation dataset, we'll increase the dialogues. Next, 50 virtual cases for the top 1–5 diseases in each subspecialty are input into the diagnostic system. If the sensitivity and specificity of specific diseases do not meet the predefined thresholds (sensitivity ≥ 90%, specificity ≥ 95%), we will proceed to develop a disease-specific image-based diagnostic system. For each disease, we will compile a dataset consisting of 50 cases, including both anterior segment images and their corresponding diagnoses. This dataset will be randomly partitioned into training and testing sets, with the training set supporting system development and the testing set assessing diagnostic accuracy. Should the predetermined criteria (sensitivity ≥ 90%, specificity ≥ 95%) be satisfied, there will be no necessity for further expansion of the sample size.

For the silent evaluation stage, the primary objective is to achieve a sensitivity ≥ 85% and specificity ≥ 95% for diagnosing ophthalmic diseases. To meet this goal, we set sensitivity = 0.85, specificity = 0.95, statistical power (1-β) = 85, significance level (α) = 0.05, and the sample size for each disease is determined to be 22, following the methodology (Tests for One-Sample Sensitivity and Specificity) outlined in Pass15. Since this stage covers at least four different illnesses, we will include a minimum of 88 patients in the entire sample. To account for potential confounding factors, we have opted to include 100 patients in this phase.

For the early clinical evaluation stage, all subjects collected within predefined date ranges at three sites will be included. Data collection at the Shanghai and Nanjing sites spans from July 21 to August 20, 2023. At the Suqian site, data collection is scheduled from August 21 to August 31, 2023.

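### Silent evaluation: 22 cases per disease at 85% power does not address the stated goal of sensitivity ≥ 85% and specificity ≥ 95%, and 100 patients do not assure 22 cases per disease

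*Protocol article*

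**What the plan says.** All of this is in the protocol article. Under Sample size calculation, for the silent evaluation, "the primary objective is to achieve a sensitivity ≥ 85% and specificity ≥ 95% for diagnosing ophthalmic diseases". To reach it, "we set sensitivity = 0.85, specificity = 0.95", with "statistical power (1-β) = 85" (evidently 85%) and "significance level (α) = 0.05". From these, "the sample size for each disease is determined to be 22, following the methodology (Tests for One-Sample Sensitivity and Specificity) outlined in Pass15". The total follows: "Since this stage covers at least four different illnesses, we will include a minimum of 88 patients in the entire sample". This is raised to 100, and the reason given is confounding.

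Under Recruitment, "data will be continuously gathered in Shanghai from July 10 to July 15, 2023, with a sample size of 100 cases". Eligibility criteria admit patients with any eye concern, apart from uncommon diseases. Statistical analysis uses a one-vs.-rest approach, so sensitivity for a disease rests on the number of patients who have it.

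**The concern.** A one-sample test sets an assumed true value against a null value. Here the goal is placed on the assumed-truth side. A test powered that way can show only that sensitivity exceeds some lower null. To show that sensitivity is at least 85%, 0.85 would have to be the null and the assumed truth would have to be higher.

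This is the only formal sample-size justification for either evaluation stage, and it is attached to a primary objective. Left as it is, it invites disease-level statements that 85% sensitivity was tested with 85% power. Separately, multiplying 22 by four secures 22 per disease only if the patients happen to divide that way.

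**Working it through.** **Inputs from the protocol.** Assumed sensitivity 0.85 and specificity 0.95, power 0.85, α = 0.05 (sidedness not stated), n = 22 per disease, at least four diseases, 100 patients. **Assumed here:** the null values, true values other than 0.85, and the disease mix.

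**1. Reproducing the plan's figures.** 22 × 4 = 88 is correct. The 22 cannot be derived from the printed inputs without a null. The normal approximation is

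n = [(z_α √(p0(1−p0)) + z_β √(p1(1−p1))) / (p1−p0)]², with p1 = 0.85 and z_β = 1.036.

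- One-sided, p0 = 0.60: [(1.645 × 0.490 + 1.036 × 0.357)/0.25]² = 22.1, so 23 (exact binomial 24).
- Two-sided, p0 = 0.55: [(1.960 × 0.497 + 1.036 × 0.357)/0.30]² = 20.1, so 21 (exact 23).
- p0 = 0.70: exact 57 one-sided, 74 two-sided.

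So 22 comes back approximately for a null near 0.55 to 0.60 and not for one near the goal.

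**2. The highest null that 22 cases can reject with 85% exact power at true 0.85.** P(X ≥ 17 | 22, 0.85) = 0.900 and P(X ≥ 18 | 22, 0.85) = 0.774, so rejection must begin at 17 or lower.

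- One-sided 0.05: P(X ≥ 17 | 22, 0.58) = 0.0498. The limit is about 0.58.
- Two-sided 0.05 (0.025 in the tail): P(X ≥ 17 | 22, 0.546) = 0.0248. The limit is about 0.546.
- At a null of 0.70, rejection needs 20/22 and power is 0.34.

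If 22 counted non-cases as well, there would be fewer diseased patients and the limit would be lower still.

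**3. Taking 0.85 as the null, n = 22.** The one-sided exact test rejects only at 22/22:

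| True sensitivity | P(22/22) |
|---|---|
| 0.85 | 0.85²² = 2.8% |
| 0.90 | 0.90²² = 9.8% |
| 0.95 | 0.95²² = 32% |

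The two-sided exact test cannot reject: 22/22 has a lower 95% limit of 0.025^(1/22) = 84.6%. For scale, 85% power against a null of 0.85 takes 319 cases one-sided if the truth is 0.90, and 68 if it is 0.95.

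**4. Taking the goal as an observed value ≥ 85%.** 0.85 × 22 = 18.7, so 19/22 is needed.

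- P(X ≥ 19 | 22, 0.85) = 57.5%
- P(X ≥ 19 | 22, 0.80) = 33%
- A true sensitivity of about 0.905 is needed for the chance to reach 85%.
- 19/22 has an exact 95% CI of 65% to 97%.

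**5. Specificity.** With 22 of 100 patients diseased, 100 − 22 = 78 are not. Showing specificity above 0.95 with 85% power takes 124 non-cases one-sided even if the truth is 0.99.

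**6. Case yield from 100 patients.** With exactly four diseases, equally common and nothing else, the mean is 100/4 = 25 each. The chance that one given disease reaches 22 is 0.79, and that all four do is 0.28 (multinomial). Five diseases at 22 each need 5 × 22 = 110 patients.

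**The case against.** - *A null must have been entered, and an article may omit it.* This stands. The missing null is not itself the fault, and 22 is not shown to be a miscalculation. What remains is that no null compatible with 22 and 85% power lies near the goal, so disclosing it would not rescue the claim.
- *With 10 subspecialties, 100 patients will clearly fall short of 22 each.* A reader might infer this, but the documents do not support it. The phrase "from 10 ophthalmic subspecialties" describes the dialogues gathered for development. The silent stage plans on at least four illnesses, and with exactly four the mean is 25. The absence of a disease quota is likewise silence in a condensed article.
- *The plan fails because all four diseases must pass together.* No such rule is stated, so a joint probability would judge the plan against a criterion it does not contain.
- *No result in 22 patients could exclude 85%.* This is true only of the two-sided exact interval. One-sided, 22/22 has a 95% lower limit of 0.05^(1/22) = 87.3%, and the protocol does not state sidedness.
- *The stage is short and preliminary.* The abstract speaks of exploring performance, and no rule makes the next stage depend on this one. That limits the consequences, but the power statement is still attached to a primary objective.

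**Conclusion.** The concern holds as a mismatch between the powered hypothesis and the stated objective; it is not an arithmetic error. Twenty-two cases per disease support showing that sensitivity exceeds about 55% to 58%, if the truth is 0.85. They do not give 85% power for a goal of 85% or more on either reading: against a null of 0.85 the chance at true 0.85 is 2.8% one-sided and nil two-sided by the exact test, and for an observed value of 85% it is 57.5%.

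The number of cases is a second, weaker part. One hundred continuously enrolled patients do not assure 22 in each of four diseases (about 28% under equal shares) and cannot give it for each of five or more. These results rest on exact binomial tests with 22 diseased cases, and the 28% on the assumed disease mix.

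**What to change.** 1. Withdraw the statement that 22 per disease gives 85% power for the ≥ 85% / ≥ 95% goal.
2. Report the null sensitivity, null specificity and sidedness actually entered, and say that the 85% power applies to that null. The authors should report their own input, not a value worked back from 22.
3. Treat disease-level sensitivity and specificity in the silent stage as descriptive, with exact confidence intervals. Judge the 85% and 95% marks with the interval shown, not by the point estimate alone.
4. State the precision that 100 patients give for the overall proportion correctly diagnosed. For example, 85/100 has an exact 95% CI of 76.5% to 91.4%. If this quantity is to be tested, the sponsor must choose and justify the null.
5. Say that 22 cases per disease is an expectation that depends on the disease mix and is not assured.

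The cost is a rewritten sample-size paragraph and a few words in the analysis section, with no extra patients. The downside is that the per-disease claim becomes descriptive.

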### Data management

The research consortium organizes a central data management board, and the contact details of its members can be obtained from the consortium coordinator, [name]. Electronic medical records data for all recruited subjects will be securely stored in password-protected files on the hospital's local server. Access to these files will be restricted to researchers with the explicit consent of the subjects. Survey data, both input and output from the multimodal AI system, will be stored in a secure public server (aliyun.com). To safeguard patient privacy, we will not collect any Protected Health Information (PHI), including the patient's name, date of birth, and medical insurance number. The anterior segment images captured by either slit-lamp or smartphones will undergo digital masking to irreversibly remove identifiable features, while preserving disease-relevant features essential for diagnosis. To further ensure data security, clinical researchers, trained in data management, will utilize password-protected smartphones for data entry. The smartphone is securely stored in a cabinet with password protection and is not permitted to be taken outside of the research site. Data integrity will be rigorously maintained through a variety of mechanisms, including referential data rules, valid values, range checks, and consistency checks against data already stored in the database.

### Adverse event monitoring

The multimodal AI system doesn't disrupt standard patient management procedures, ensuring the integrity of diagnosis and treatment. Patients in the study also benefit from thorough medical history reviews by five expert clinicians, enhancing the standardization of their care. The major adverse events may stem from biased outputs and misinformation produced by language models. All participants (including researchers) in this study are encouraged to report any toxic information generated by the multimodal AI system, such as unhelpful information that fails to assist users in their tasks, dishonest information that fabricates or misleads users, and harmful information that can lead to physical, psychological, or social harm to individuals or the environment. In our prompt engineering process, we will include a fine-tuning phase to iteratively enhance content quality. Collecting toxic content is helpful for identifying areas for improvement and making necessary adjustments. Therefore, the fine-tuning process based on toxic content may facilitate adapting our AI system to real-world use and mitigating potential harms.

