### Outcome measure

The primary outcome is the correctness of the AI system's diagnosis, and the secondary outcome is the correctness of the AI system's triage decisions. The above assessment takes place by comparing the AI-generated results with the reference standards established by expert panels:

(1) Judged as correct: when the system's results are entirely consistent with the reference standard; when the system's results fall within the range of the reference standard.(2) Judged as incorrect: when there is no overlap between the system's results and the reference standard; when the system fails to provide any diagnostic or triage information.(3) In the following scenarios, additional discussion and assessment are required. A consensus is considered to be reached when at least 2 out of 3 experts are in agreement: when the reference standard includes the system's results; when there is partial overlap between the system's results and the reference standard.

In addition to assessing accuracy, we will also evaluate the quality, empathy, and patient satisfaction of the AI system's responses. Three independent evaluators (licensed healthcare professionals), who are blinded to the accuracy of the responses, will judge both “the quality of information provided” (very poor, poor, acceptable, good, or very good) and “the empathy of information provided” (not empathetic, slightly empathetic, moderately empathetic, empathetic, and very empathetic) on a scale of 1–5. Notably, these quality and empathy rating assessors evaluate the quality and empathy of the AI results based solely on the AI output, without knowledge of the patient's complete clinical information, reference standard results, or the correctness of the AI output.

During the early clinical evaluation stage, patient satisfaction (not satisfied, slightly satisfied, moderately satisfied, satisfied, and very satisfied) will be measured on a scale of 1–5 after AI responses have been generated. When evaluating satisfaction of the AI output, the patients are only aware of the AI output and remain uninformed about the reference standard results or the correctness of the AI output. After the evaluation, they can be informed of the reference standard results and the correctness of the AI output.

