### Blinding

The blinding methods vary depending on the roles of the researchers and the stage of the study in which the researchers and subjects are involved. AI developers and AI output correctness assessors have access to complete patient information, including medical history, reference standard results, and AI output for determining correctness.

In our study, two roles are subject to blinding. (1) Reference standard assessors: These assessors possess knowledge of the patient's clinical information but are unaware of the AI output or its correctness. This approach helps mitigate information bias and classification bias. (2) Clinical researchers: These researchers are responsible for inputting data into the multimodal AI program. During the *in silico* development stage, they have access to all patient clinical information and reference standard results. However, during the silent evaluation and early clinical evaluation stages, they only have access to the patient's clinical information without knowledge of the reference standard. This approach helps mitigate diagnostic suspicion bias.

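### Misinformation is named as the main adverse event but captured only by voluntary report, and outputs judged incorrect are not screened for harm

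*Protocol article*

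**What the plan says.** The section on adverse event monitoring in the protocol article identifies the harm of interest: "The major adverse events may stem from biased outputs and misinformation produced by language models". It then gives one way of collecting it: "All participants (including researchers) in this study are encouraged to report any toxic information generated by the multimodal AI system". Reportable content is defined broadly and includes "dishonest information that fabricates or misleads users", as well as unhelpful content and content that can cause harm. The reports are to feed the fine-tuning of the system. The Discussion adds that documenting such content is regarded as important.

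Who knows what is set out elsewhere. The Blinding section states "In our study, two roles are subject to blinding": the reference standard assessors, who do not see the AI output, and the clinical researchers. Of the latter, in both evaluation stages, it says "they only have access to the patient's clinical information without knowledge of the reference standard". The Implementation section makes these researchers junior university students of clinical medicine. Under Outcome measure, when patients rate satisfaction in the early clinical stage, "the patients are only aware of the AI output and remain uninformed about the reference standard results or the correctness of the AI output". In contrast, "AI developers and AI output correctness assessors have access to complete patient information, including medical history, reference standard results, and AI output for determining correctness".

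The same Outcome measure section asks the assessors to decide whether diagnosis and triage are correct. It sends unclear cases to a discussion settled by two of three experts, and it contains no question about harm.

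**The concern.** A voluntary report depends on someone noticing that something is wrong. Offensive or useless text is easy to notice. A fluent, credible but wrong answer is not, and that is the kind of misinformation the section puts first. If those who see the output in use cannot recognise it, and those who can are never asked about harm, the adverse event record will lean towards conspicuous failures.

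Two things are at stake. First, the planned mitigation learns from reported content, so it would learn little from plausible errors. Second, the Discussion foresees some patients with minor or non-urgent conditions bypassing direct physician evaluation. In that setting a credible wrong answer matters most, and a short list of spontaneous reports would say little about it.

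**Working it through.** The article states no adverse event count or rate, so there is no figure to reproduce. The check sets each role's knowledge beside its task.

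- **Student researchers (both evaluation stages).** They enter the data and see the output, but do not know the reference standard (Blinding, Implementation). They may report if they notice something.
- **Patients (early clinical stage).** They see the output and rate it without knowing its correctness; afterwards they can be told (Outcome measure). They may report.
- **Reference standard assessors.** They know the diagnosis but do not see the output (Blinding), so they cannot recognise a misleading one.
- **Quality and empathy evaluators.** They are licensed professionals who see the output without the full clinical information, the reference standard or correctness (Outcome measure). They can spot implausible text, but not an answer that is plausible and wrong for that patient.
- **Correctness assessors.** They hold the history, the reference standard and the output (Blinding). They judge diagnosis and triage once data collection is complete (Early clinical evaluation). They may report, but no harm question is put to them.
- **AI developers.** They have the same access and may report, with no required task of this kind.

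So one panel has both the knowledge and a systematic task, and the harm definitions are not part of that task. No section passes an output judged incorrect on to adverse event recording.

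For scale only, take the silent evaluation: n = 100 cases (Recruitment) and a sensitivity target of 0.85 (Hypotheses). Assume that overall correctness equals that target, which would follow if each case carried one diagnosis and every disease sat exactly at the target.

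- Expected wrong diagnoses: n × (1 − 0.85) = 100 × 0.15 = 15, with a 95% binomial range of 8 to 22.
- At the early clinical target of 0.75, per 100 outputs: 100 × 0.25 = 25, range 17 to 34.
- If a fraction r of the 15 were reported, the record would hold 15r: 1.5 at r = 0.10, 7.5 at r = 0.50, 15 at r = 1.

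The undercount is 1 − r, that is 90%, 50% and 0%. It is only the complement of an assumed r, on which the documents are silent. The calculation also treats every wrong diagnosis as reportable, which the article does not say.

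**The case against.** The strongest reply is that the invitation to report excludes nobody. It covers developers and correctness assessors, who know which outputs are wrong. Patients can be told the result after their rating, and in the early clinical stage the outpatient physician makes a diagnosis soon after data collection, so a patient may notice a discrepancy. No deadline bars a late report. This stands. A reader might infer that only people kept unaware of correctness can report; the documents do not support that. What remains is that reporting is voluntary for the informed roles too, and nothing prompts it.

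A second reply is that wrong outputs are not lost: among analysed cases, every incorrect diagnosis and triage decision enters the primary or secondary outcome. This also stands. But an error count does not separate a harmless mislabel from a misleading or dangerous answer, which is the distinction the adverse event definitions draw.

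A reader might also infer that the assessors already identify every wrong output. They do not. They judge diagnosis and triage, not other text, and cases with a program error or without a definitive diagnosis after 3 months are excluded.

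Finally, a condensed article may leave forms and adjudication to the full protocol. That is fair for missing detail. Here, however, the article does state a method, and the point concerns that method. The full protocol may add to it.

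**Conclusion.** The point holds in a limited form: a cheap improvement, held with medium confidence. The stated capture method is weakest for the harm the section names first, and the panel best placed to recognise that harm is not asked about it. Under-recording of plausible but misleading output is therefore likely. Its size is not derivable; the illustration spans everything from no undercount to 90%, depending wholly on an assumed reporting rate.

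A reader might go further and call adverse events structurally undercounted by a known share, or expect a low count to be presented as proof of safety. Neither follows. No adverse event rate or safety endpoint is planned in the article, and it does not define an incorrect diagnosis as an adverse event.

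The conclusion assumes that the full protocol adds no systematic harm review, and that voluntary reports by the informed roles will be incomplete.

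**What to change.** In the sections on outcome measure and adverse event monitoring, require the existing correctness assessors to record two further items for each output judged incorrect or partly overlapping: (a) whether it was fabricated or misleading, and (b) whether it was potentially harmful if acted on. They would use the definitions already given for adverse events. The two-of-three rule, which now settles unclear cases, should be extended to these two items.

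Report both counts over all outputs assessed, by stage and site, and state how many cases were excluded before assessment. Keep voluntary reports as a supplement, because harmful text that accompanies a correct diagnosis would not pass through this screen.

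The cost is two form fields, one table and a little more assessor time, with no extra patients. The reported safety figure will probably look less favourable than a list of spontaneous reports.
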